### Effect and Sample Size

We conducted a power calculation for the main outcome: the proportion of patients with first-episode psychosis who, by their treating clinician’s or their own decision, discontinue, for any reason, the first prescribed antipsychotic medication within 1 year. As stated previously, recent research studies, mostly carried out in early intervention settings, concur that 40% of patients with first-episode psychosis experience first prescribed antipsychotic drug discontinuation during the first year following treatment initiation [7,8]. This proportion may be even higher in patients receiving mainstream psychiatric care, such as our cohort 2. Considering the expectations behind the use of personalized precision medicine, PRINT should aim to reduce discontinuation rates to 10%. Therefore, for a power of 80% with (1) a significance level of .05 (2-sided), (2) all-cause discontinuation rate in cohort 1 (intervention) of 0.4, (3) all-cause discontinuation rate in cohort 2 (treatment as usual) of 0.1, and (4) an expected dropout or loss to follow-up rate of 0.2, our calculations would require a sample size of at least 38 patients in each cohort. We used the R statistical software *pwr* package for this calculation (version 4.4.2 for Windows; R Foundation for Statistical Computing).

In CAUSA, we have found an administrative incidence of 50 new patients aged 12 to 35 years every year. Thus, we would expect at least 75 patients eligible to be recruited for cohort 1 over 18 months. Using a conservative approach, if 25 patients (approximately 35%) do not agree to take part, we would still enroll 50 patients. This would be in addition to another 50 patients in our retrospective cohort 2 and pharmacogenetic data currently available at CAUSA from 100 patients with psychotic disorders of more than 5 years of evolution and another 100 patients with other mental disorders that we shall use for further comparative purposes, as outlined previously. This all accounts for a total of 300 participants contributing to this project.

### Statistical Analysis

Comparisons of the main outcome (ie, discontinuation rates) will be carried out using the chi-square test. Kaplan-Meier survival curves and multivariate log rank tests will be used to assess time to all-cause antipsychotic discontinuation. For these analyses, patients will be followed up on for a year, from antipsychotic treatment initiation until discontinuation. Thus, we shall censor survival time by the end of the 1-year observation period or before such date if there is enough evidence of antipsychotic discontinuation. We shall describe and compare sociodemographic information and clinical and functional outcomes within and between groups. Means and SDs will be used to describe quantitative variables. We shall use the chi-square test or Fisher exact test for categorical variables and Mann-Whitney *U* test for continuous variables, among others. Data analyses will be conducted using the R statistical software (version 4.4.2 for Windows).

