### Participants

A total of 300 patients will be included in this project. We shall include 2 different cohorts. Cohort 1 will be a prospective sample of patients with first-episode psychosis referred over 18 months to the new early intervention in psychosis program of personalized precision psychiatry (PRINT) at CAUSA. Cohort 2 will be a retrospective, consecutive (in reverse chronological order as registered in the CAUSA electronic health records) sample of patients who experienced a first episode of psychosis before the implementation of PRINT.

Inclusion and exclusion criteria for both cohorts will be aligned with the PRINT program referral acceptance criteria, which are predominantly inclusive.

Inclusion criteria are as follows: patients (1) with a diagnosis of first-episode psychosis, either nonaffective or affective; (2) aged 12 to 35 years; and (3) followed by clinical services for at least 1 year or earlier if there was evidence of antipsychotic treatment discontinuation (see the Outcome Measures section). In addition, patients in cohort 1 or their family or legal representatives will have to provide written consent to take part in the CLUMP project, including pharmacogenetics analysis (see the Ethical Considerations section). For patients in retrospective cohort 2, this will not be an inclusion criterion, but all of them will be approached by our research team seeking their consent to obtain their pharmacogenetic profile for research purposes.

Exclusion criteria are as follows: patients (1) with first-episode psychosis due to organic causes, for example, brain diseases such as Huntington or Parkinson disease, HIV, syphilis, dementia, brain tumors or cysts, or brain injury; (2) with moderate to severe intellectual disability; and (3) who spent (cohort 2) or plan to reside during (cohort 1) most of the 1-year follow-up period in a locality out of the PRINT program’s catchment area.

For additional comparative purposes, we shall analyze the environmental, clinical, and pharmacogenetic information of patients with psychotic disorders of more than 5 years of evolution or with other mental disorders whose data are currently stored and have been ethically approved for research use in our unit of pharmacogenetics and precision medicine at the HUS.

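### The primary comparison of two non-randomised cohorts is fixed as an unadjusted chi-square test, so measured case-mix differences pass into the primary result

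*Protocol article*

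**What the plan says.** The two groups are formed by period, not by randomisation. In the Participants section, "Cohort 1 will be a prospective sample of patients with first-episode psychosis referred over 18 months", under the new programme, while "Cohort 2 will be a retrospective, consecutive (in reverse chronological order as registered in the CAUSA electronic health records) sample of patients" whose first episode came before PRINT began. Cohort 2 was treated by generic community teams (Clinical Management and Pharmacogenetics Analysis). Other inclusion and exclusion criteria are shared.

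Consent is handled differently in the two cohorts. The Participants section says that "patients in cohort 1 or their family or legal representatives will have to provide written consent to take part in the CLUMP project", and then: "For patients in retrospective cohort 2, this will not be an inclusion criterion". Cohort 2 patients are approached later for consent to genotyping. Ethical Considerations, by contrast, states that written consent is obtained from all participants. On refusal in cohort 1, Effect and Sample Size gives a conservative scenario: "if 25 patients (approximately 35%) do not agree to take part, we would still enroll 50 patients".

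The Statistical Analysis section sets the methods. For the primary outcome: "Comparisons of the main outcome (ie, discontinuation rates) will be carried out using the chi-square test". For time to event: "Kaplan-Meier survival curves and multivariate log rank tests will be used to assess time to all-cause antipsychotic discontinuation". The other use of baseline data is: "We shall describe and compare sociodemographic information and clinical and functional outcomes within and between groups". No covariate, stratum, matching, weighting or regression model is named. The Limitations section covers the single centre and status quo bias. It does not mention confounding, calendar period or selection by consent.

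**The concern.** A chi-square test on two proportions compares like with like only if the groups are exchangeable apart from the exposure. Here nothing in the design makes them so beyond shared eligibility criteria and catchment area. If the cohorts differ in age, sex, or the mix of affective and nonaffective psychosis, and those factors predict discontinuation, the difference is credited to the programme. The economic evaluation uses the same outcome, so the bias would reach it too.

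If consent is required only in cohort 1, that cohort is also filtered by willingness to take part, in a study whose primary outcome measures adherence. That could lower the cohort 1 discontinuation rate with no effect of the programme.

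This is not a detail left open for an analysis plan. The article makes a positive choice of the primary test, and that test is unadjusted.

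**Working it through.** **1. The plan's own figure.** Inputs from Effect and Sample Size: rates 0.4 and 0.1, two-sided 0.05, power 80%, loss 20%. With the arcsine effect size used by the R pwr package:

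- h = 2·asin(√0.4) − 2·asin(√0.1) = 0.726
- n = 2·((1.960 + 0.842)/0.726)² = 29.8, rounded up to 30
- 30/(1 − 0.2) = 37.5, rounded up to 38 per cohort

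The stated 38 is reproduced. Power for 0.4 against 0.1 is 94.6% at 50 against 50 and 88.8% at 40 against 40 (50 × 0.8 = 40). The problem is therefore bias and not lack of power.

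**2. False-positive rate under a case-mix gap.** The assumptions, none of them in the documents, are: no treatment effect, a true cohort 2 rate of 0.40, and a cohort 1 rate lower only because of case mix. Reject when |p̂₁ − p̂₂| / √(p̄(1 − p̄)(1/n₁ + 1/n₂)) > 1.96, and sum the product of the two binomial probabilities over all rejecting tables (exact enumeration). The continuity-corrected version subtracts ½(1/n₁ + 1/n₂) from the absolute difference.

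| Cohort 1 rate | Gap | 50 v 50 | 50 v 50, corrected | 40 v 40 | 40 v 40, corrected |
|---|---|---|---|---|---|
| 0.40 | 0 | 5.2% | 3.2% | 5.2% | 3.0% |
| 0.30 | 10 points | 18.0% | 13.2% | 15.2% | 10.4% |
| 0.25 | 15 points | 35.8% | 28.7% | 29.4% | 22.1% |

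**3. Consent selection alone**, if the Participants text stands. Take the conservative scenario of one third declining (25/75) and an all-comer rate of 0.40. If decliners discontinue RR times as often as consenters (RR assumed), the consenters' rate is c = 0.4/(2/3 + RR/3).

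- RR = 1.5: c = 0.4/1.167 = 0.343, rejection 9.1% at 50 against 50 (uncorrected)
- RR = 2: c = 0.4/1.333 = 0.300, rejection 18.0%

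**4. Events available for adjustment.** On the plan's target of 10% under PRINT and 40% otherwise: 0.1 × 50 = 5 events in cohort 1 and 0.4 × 50 = 20 in cohort 2, 25 in all. The sample-size sentence attaches these two rates to the opposite cohorts, but the text just before it gives 10% as the PRINT target. This limits how many covariates an adjusted analysis can carry.

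**The case against.** Several points on the other side stand.

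- A reader might infer that the plan expects a third of eligible patients to refuse. It does not: the 25 of 75 is a conditional, cautious scenario.
- A reader might take it as settled that consent is needed in one cohort only. The Participants section says so, but Ethical Considerations says otherwise. Relatives or legal representatives may also consent, which weakens the link between consent and the patient's own adherence.
- A reader might list the change of service as a confounder. It is not: the hypothesis concerns PRINT with 5SPM built in, and generic care is the comparator, so service is part of the exposure.
- A reader might say that the multivariate log rank test is certainly unadjusted. The term is ambiguous and could mean a stratified test, whose p-value would be adjusted. But no strata are named, it would give no adjusted effect estimate, and it would leave the chi-square on proportions unchanged.
- Shared eligibility and catchment criteria, and sampling backwards from the most recent pre-PRINT patients, limit case-mix and calendar drift. They do not balance the cohorts.
- The case-mix gaps and relative risks above are illustrative. The documents give no figure for confounding strength, and continuity correction or attrition lowers the rejection rates.

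None of this removes the central point: the article names an unadjusted primary comparison for a historical-control design.

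**Conclusion.** The concern holds in this form. The Statistical Analysis section commits the primary outcome to an unadjusted test of two non-randomised cohorts from different periods, and nothing else named there yields an adjusted effect, so measured case-mix differences remain in the primary result. The consent statements conflict and must be reconciled; if consent is an inclusion criterion for cohort 1 only, selection by consent is an additional bias.

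The actual size is unknown. On the assumed inputs, a 10-point gap raises the false-positive rate from about 5% to 18% (13% corrected; 15% uncorrected at 40 against 40), and a 15-point gap raises it to 36% (29% corrected; 29% uncorrected at 40 against 40). These show how sensitive the test is; they do not predict that the result will be false.

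Nor do the documents support reading adjustment as a full cure. Calendar period coincides with cohort, and willingness to consent is not a measured covariate, so neither can be balanced by weighting or regression.

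**What to change.** 1. Make the primary estimate a prespecified covariate-adjusted difference in 12-month discontinuation risk with a 95% CI, for example by propensity weighting, and state the target population that the weights imply. Report the chi-square as the unadjusted result.
2. Replace the multivariate log rank test with a correspondingly adjusted Cox model.
3. Fix a short list of pre-index covariates available in both cohorts: age, sex, and affective or nonaffective diagnosis. Inpatient status at index and substance use are not named as planned variables; add them only if they are confirmed to be available in cohort 2 records. Do not adjust for the antipsychotic chosen, because 5SPM acts through it.
4. Reconcile the Participants and Ethical Considerations sections on consent in cohort 2.
5. State as limitations that adjustment cannot remove calendar period or consent selection. An analysis restricted to cohort 2 genotyping consenters should be exploratory only: that consent is sought after the outcome, so reachability and agreement may depend on it.

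The cost is mainly wording and analysis code, plus a check of cohort 2 records if further covariates are wanted. The downside is some loss of effective sample size and fragile estimates from few events in cohort 1 (about 5 on the plan's rates), which is why the list must be short. It should be fixed before outcomes are compared; the Results section puts the end of data collection at June 2027.

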### Outcome Measures

#### Primary Outcome Measure

The primary outcome to measure treatment adherence will be all-cause discontinuation of the initially prescribed antipsychotic medication following the patient’s or treating clinician’s decision. All-cause discontinuation rates in the CLUMP project will be defined by all-cause discontinuation proportions during the 1-year follow-up and the mean time to such discontinuation.

For cohort 1, the 1-year follow-up period will start when an antipsychotic medication is prescribed taking into consideration the pharmacogenetics advice emerging from the 5SPM method. For cohort 2, follow-up would begin on the date when the first antipsychotic medication was prescribed. For both cohorts, the first prescribed antipsychotic will be the initially prescribed antipsychotic drug for maintenance treatment, not only for short-term use to control psychomotor agitation. In addition, in accordance with existing scientific consensus, the discontinuation date will be defined as the first day of a 2-week or longer interruption of the first prescribed antipsychotic. In cohort 2, treatment discontinuation dates will be determined by examining clinical records. Where only approximate dates are available, the first, middle, or final day of the month will be used as best estimates. In cases in which cross-titration of medication took place, the date of discontinuation will be the first day of the cross-tapering process.

All-cause discontinuation will also be stratified by 4 reasons: insufficient efficacy, adverse events, lack of adherence, and other. Insufficient efficacy will be established at the treating clinician’s judgment only after at least 3 weeks of treatment. If more than one reason for discontinuation was present, we shall select one by applying the ranking order as stated previously.

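### The survival analysis names discontinuation, its own event, as a reason to censor, and the primary outcome includes a mean time to discontinuation with no 12-month restriction

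*Protocol article*

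**What the plan says.** The Statistical Analysis section assigns time to all-cause discontinuation of the first antipsychotic to Kaplan-Meier curves and log-rank tests, and follows patients for a year or until they discontinue. Its one sentence on censoring says the investigators "shall censor survival time by the end of the 1-year observation period or before such date if there is enough evidence of antipsychotic discontinuation".

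The Primary Outcome Measure section defines the primary outcome by "all-cause discontinuation proportions during the 1-year follow-up and the mean time to such discontinuation". It dates the event fully: the first day of a break of two weeks or more or, where drugs are cross-titrated, the first day of the cross-taper. It does not say how the mean is to be calculated or over what window.

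Three other places bear on the point:

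- The Abstract gives the 1-year proportion alone as the primary outcome. Effect and Sample Size powers the study on that proportion, and Statistical Analysis tests it by chi-square.
- Effect and Sample Size allows for "an expected dropout or loss to follow-up rate of 0.2".
- Inclusion criterion 3 under Participants requires at least 1 year of follow-up by clinical services, or less if the antipsychotic was discontinued.

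**The concern.** In a time-to-event analysis the event ends a patient's time and is counted; censoring ends it without being counted. The censoring sentence gives two reasons to censor: reaching 1 year and discontinuing. The second is the event. The patients who do need early censoring, those lost while still taking the drug, are not mentioned.

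The mean time is a separate problem. When many patients have not had the event by the end of the window, the data do not determine their mean time to it. An analyst must then extrapolate, average only those who discontinued, or restrict the mean to the window. These give very different answers, and the plan does not choose. The section's general tools for quantitative variables (means with SDs, Mann-Whitney) take no account of censoring if applied to this time.

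The comparison is not randomised and the retrospective cohort's outcomes already exist. Leaving the censoring rule and the estimator open means they could be settled after outcomes are known.

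**Working it through.** **Inputs.** From Effect and Sample Size: two-sided 5% level; 80% power; a 1-year discontinuation rate of 40% ("40% of patients with first-episode psychosis experience first prescribed antipsychotic drug discontinuation during the first year following treatment initiation"); a target of 10% under PRINT; 20% loss; 50 patients planned per cohort. That section attaches the 40% and 10% to the cohorts in the reverse of its own rationale. This does not change a two-sided sample size, and below I refer to the groups by their rates. Exponential times to discontinuation are my assumption; the protocol gives no distribution.

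**1. The plan's own figure.** Arcsine effect size h = 2·asin(√0.4) − 2·asin(√0.1) = 0.726. Then n = 2·((1.960 + 0.842)/0.726)² = 29.8, so 30. With 20% loss, 30/0.8 = 37.5, so 38. This reproduces "a sample size of at least 38 patients in each cohort". It rests on the proportion only.

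**2. The censoring sentence taken literally.** Expected discontinuations are 50 × 0.4 = 20 and 50 × 0.1 = 5, 25 in all. If all 25 are coded as censored there are no events, both curves stay at 1, and the log-rank statistic is 0/0. With discontinuation coded as the event and censoring at 12 months, the hazard ratio is ln(0.9)/ln(0.6) = 0.21. Simulated log-rank power (2,000 runs) is then about 96% with 50 per cohort and 90% with 40.

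**3. Patients lost on the drug.** If the 20% applied to 50 enrolled, about 10 patients per cohort would be lost. The protocol does not say how many of them would still be on the drug, and the censoring sentence gives no instruction for them.

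**4. The mean time.** With p the 1-year rate and L = −ln(1 − p) per year, L = 0.511 for 40% and 0.105 for 10%.

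| Quantity (months) | Formula | 40% rate | 10% rate | Difference |
|---|---|---|---|---|
| Unrestricted mean (extrapolated) | 12/L | 23.5 | 113.9 | 90.4 |
| Mean among discontinuers | 12·(1/L − (1 − p)/p) | 5.49 | 5.89 | 0.40 |
| Restricted mean to 12 months | 12·p/L | 9.40 | 11.39 | 1.99 |

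The unrestricted means lie far outside a 12-month window: 60% and 90% of patients are event-free at its end. In the simulation with 50 per cohort, a simple comparison of the discontinuers' means passed 1.96 standard errors in about 12% of runs. The 10% group contributes about 5 patients to it.

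**5. Dependence on the exponential assumption.** Whatever the distribution, with follow-up complete to 12 months the restricted mean equals 12·(1 − p) + p·m, where m is the mean time among discontinuers. Check: 7.2 + 0.4 × 5.49 = 9.40 and 10.8 + 0.1 × 5.89 = 11.39. If m is the same in both groups, the discontinuers' means do not differ at all, while the restricted means differ by 3.6 − 0.3·m: 2.7 months at m = 3, 1.8 at m = 6, 0.9 at m = 9.

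**The case against.** **The censoring sentence is a slip.** The text just before it makes discontinuation the endpoint and ends follow-up there, the sentence itself opens as a consequence of that, and the detailed dating of the event would serve no purpose if the event were censored. This stands. A reader might infer that the analysis will be run with no events and an undefined log-rank test; the documents do not support that as the intention. What remains is that the only stated censoring rule is wrong as written.

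**Criterion 3 explains the silence on losses.** A patient lost before 1 year without discontinuing does not meet it, so on that reading nobody needs early censoring. This is fair, and the fix must deal with it. But cohort 1 is prospective, so the criterion cannot be checked at enrolment. Applying it later removes patients because of what happened during follow-up. It also sits badly with a planned 20% loss.

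**The mean can be estimated.** Observation is capped at 1 year, so a mean limited to 12 months is available, and no text commits to an unrestricted one. It would be too strong to say the measure cannot be rescued. How to compute a mean is often left to an analysis plan, but this one is written into the primary outcome, and two of its natural readings fail.

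**Most patients never discontinue.** This might be inferred from the 60% and 90%, but the documents support only no discontinuation within 1 year. The Introduction cites 80% after 3 years, and the sample-size section allows that standard care may exceed 40%. The 10% is a target.

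**The main test is untouched.** Correct: neither the chi-square comparison nor the sample size depends on the wording at issue.

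**Conclusion.** The point holds in two limited parts.

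First, the censoring sentence contradicts the endpoint it serves. Followed literally it would discard all of about 25 expected events. It also leaves patients lost on the drug without a rule. The context points to a wording error, so this is a correction to make before analysis and not evidence of a failed design.

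Second, the mean time in the primary outcome needs a 12-month restriction. Without one it is either not identified or, if taken among discontinuers, almost blind to the planned effect: a 0.4-month gap where the hazard ratio is 0.21. The 12-month restricted mean differs by about 2.0 months.

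The month figures rest on the planning rates and exponential times. The 60% and 90% event-free rest on the planning rates alone. A reader might conclude that the primary test or the 38 per cohort is undermined; neither is.

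**What to change.** 1. In Statistical Analysis, state that discontinuation, dated as in Primary Outcome Measure, is the event, and that patients without it are censored at 1 year or at last documented contact on the drug, if earlier.
2. Reconcile inclusion criterion 3 with that rule and with the 20% loss, so that patients lost early are censored and not excluded after the fact.
3. In Primary Outcome Measure, replace the mean time by the restricted mean time on the first antipsychotic to 12 months (the area under the Kaplan-Meier curve), with its difference and 95% CI. Label it secondary to the 1-year proportion, in line with the Abstract and Effect and Sample Size.

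The cost is a few sentences in three sections, with no change to the calculated sample size. Items 1 and 3 need no new data. Item 2 needs the last contact date on the drug for patients lost early, and is the only item that touches eligibility.
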